### Research Aims and Hypotheses

#### Quantitative Aims and Hypotheses

The primary aim is to quantitatively assess patient-reported contraceptive nonuse (yes or no) at 3 months (primary outcome).

Hypothesis 1: Contraceptive nonuse will be less likely in the intervention arm than the control arm at 3 months.

The secondary aim is to quantitatively assess the Medical Eligibility Risk category for patient-reported contraceptive method use per the US MEC schema (Category 1=no risk; Category 2=Advantages generally outweigh theoretical or proven risks; Category 3=Theoretical or proven risks usually outweigh advantages; Category 4=unacceptable health risks) [7]. Clinically translated, Categories 1 and 2 indicate methods that are safe to use, Category 3 indicates methods that should be avoided unless more appropriate methods are not available or acceptable to the patient, and Category 4 indicates methods that should be avoided [7]. We will explore the potential impact of the intervention on contraceptive decisions across US MEC categories using qualitative and mixed methods analysis, with a focus on Category 3 cases.

Hypothesis 2: Given the need for a careful and informed discussion to weigh the benefits and risks of Category 3 use, we hypothesize that the decision tool will facilitate this process, leading to more Category 3 use cases in the intervention arm than the control arm.

The exploratory aim is to quantitatively explore contraception decisional conflict measured via a modified Decisional Conflict Scale (DCS) [29], and the patient-reported quality of interaction with their contraceptive provider, as measured via the Interpersonal Quality of Family Planning Scale (IQFP) [30], as mediators of the effects of MHMC on the primary outcome.

Hypothesis 3: The impact of MHMC on contraceptive nonuse will be mediated by lower DCS scores and higher IQFP scores.

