### Power and Quantitative Sample Size

The primary outcome is the proportion of participants reporting contraceptive nonuse at 3 months. Based on national estimates [10,11,43,44] and our screening protocol, we anticipate 30% (217/726) of participants at baseline will report contraceptive nonuse. A previous cluster RCT of a contraceptive decision tool in outpatient clinics found a clinic-level intracluster correlation (ICC) of 0.02 [16]. We conservatively estimate an ICC of 0.05. Prior studies have estimated ICCs generally <0.04 for patient-reported outcomes in maternal health and sexual behavior among reproductive-aged women [45-47]. To reduce our estimated ICC, we have taken several precautions. At the design level, we have defined clinic, patient, and clinician eligibility criteria to reduce heterogeneity and variance in estimates [48]. At the analysis level, we will conduct regression adjustment for key covariates [48]. To detect a difference of 20% in the proportion of contraceptive nonuse between the intervention arm and the control arm at 3 months, an effect size consistent with that of prior contraceptive trials [20,49,50], we will need to enroll 14 clinics (7 in each arm) and 45 participants in each clinic. Assuming an attrition rate of 15%, our enrollment goal is 726 patients (363 patients in each arm). We anticipate that we will enroll 5-10 clinicians per clinic, for a maximum total of about 140 clinicians. The allocation ratio will be 1:1 with attention to the balance of obstetrics and gynecology clinics in each arm, which will mitigate the impact of unequal distribution of sites that provide higher volume or scope of contraceptive services.

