### Quantitative Outcomes and Analysis

The primary outcome is contraceptive nonuse at 3 months per patient self-report, consistent with prior contraceptive studies [10,51,52]. Individual contraceptive nonuse will be modeled as a binary outcome. We will use mixed-effects nested logistic regression to assess differences in 3-month outcomes between the study arms. The model will include an arm assignment categorical covariate and will be adjusted using patient-level covariates (baseline contraceptive nonuse, education, race, ethnicity, and parity) and clinician-level covariates (self-reported experience with contraceptive care and specialty type). Random intercepts for the clinic and for clinicians nested within the clinic will account for the clustering. Secondary analyses of contraceptive nonuse will include the same model with 1-month data and a subgroup analysis that only includes patients at risk for pregnancy, that is, those who report penile-vaginal sexual activity at 1 month and 3 months.

The secondary quantitative outcome is patient-reported contraceptive method use as classified by the US MEC. We will summarize US MEC Categories 1, 2, 3, or 4 among patients who report contraceptive use at 1 month and at 3 months with descriptive statistics. Chi-square tests will be calculated to compare frequencies between the intervention group and the usual care group.

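### The US MEC comparison is confined to patients using a method at follow-up, so randomization does not protect it and it does not directly address Hypothesis 2

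*Protocol article*

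**What the plan says.** Under Quantitative Outcomes and Analysis, the article sets both the population and the test for the secondary outcome: "We will summarize US MEC Categories 1, 2, 3, or 4 among patients who report contraceptive use at 1 month and at 3 months" and "Chi-square tests will be calculated to compare frequencies between the intervention group and the usual care group". The summary is described as descriptive. No analysis of Category 3 use over all patients in each arm is stated, and the restriction to users carries no caveat.

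Under Quantitative Aims and Hypotheses, Hypothesis 2 expects the tool to support a careful discussion, "leading to more Category 3 use cases in the intervention arm than the control arm". Hypothesis 1 in the same section reads: "Contraceptive nonuse will be less likely in the intervention arm than the control arm at 3 months".

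The secondary analyses of nonuse include "a subgroup analysis that only includes patients at risk for pregnancy, that is, those who report penile-vaginal sexual activity at 1 month and 3 months".

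**The concern.** Whether a patient is a user at 1 or 3 months is known only after allocation, and it is the primary outcome seen from the other side. The better the tool works on Hypothesis 1, the more the intervention arm's user group contains people who would have been nonusers under usual care and who have no counterpart among control users. A difference in category shares between the two user groups then mixes two things: what the tool does to method choice, and who has entered the denominator.

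Hypothesis 2 is worded as more cases in one arm than in the other, whereas the planned comparison is of shares among users. The two can disagree, even in sign. The trial could then report that Category 3 use was lower with the tool when it was unchanged or higher per patient.

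**Working it through.** **Inputs from the article (Power and Quantitative Sample Size)**

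- Baseline nonuse: "we anticipate 30% (217/726) of participants at baseline will report contraceptive nonuse". Check: 217/726 = 0.299.
- Effect: "To detect a difference of 20% in the proportion of contraceptive nonuse between the intervention arm and the control arm at 3 months". Absolute or relative is not stated.
- Size: 7 clinics × 45 = 315 patients per arm before the attrition allowance.

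The article gives no expected Category 3 rate, so there is no planned figure to reproduce for this comparison.

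**Assumptions**

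- Control nonuse stays at 30% at 3 months, so the control user fraction is u0 = 0.70.
- The intervention user fraction is u1 = 0.90 if the 20% is absolute (nonuse 10%), or 0.76 if it is relative (nonuse 0.30 × 0.80 = 24%).
- Patients who would use a method in either arm keep the same Category 3 share, c. Patients moved from nonuse to use have Category 3 share a. Nobody moves from use to nonuse. The values of c and a are illustrative.

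**Formulas for the intervention arm**

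- Category 3 per patient = u0·c + (u1 − u0)·a (control: u0·c)
- Category 3 share among users = [u0·c + (u1 − u0)·a] / u1 (control: c)

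When u1 > u0, the share among users falls whenever a < c, and use per patient rises whenever a > 0. For any a between 0 and c the two measures therefore move in opposite directions.

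**Results (control → intervention)**

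| c | a | u1 | Share among users | Per patient |
|---|---|---|---|---|
| 10% | 0% | 0.90 | 10% → 0.07/0.90 = 7.8% | 7.0% → 7.0% |
| 10% | 0% | 0.76 | 10% → 0.07/0.76 = 9.2% | 7.0% → 7.0% |
| 20% | 10% | 0.90 | 20% → 0.16/0.90 = 17.8% | 14% → 0.14 + 0.02 = 16% |
| 20% | 10% | 0.76 | 20% → 0.146/0.76 = 19.2% | 14% → 0.14 + 0.006 = 14.6% |
| 10% | 10% | 0.90 | 10% → 10% | 7.0% → 9.0% |
| 10% | 10% | 0.76 | 10% → 10% | 7.0% → 7.6% |
| 10% | 30% | 0.90 | 10% → 0.13/0.90 = 14.4% | 7.0% → 13% |

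With 315 patients per arm, the third row is 0.14 × 315 = 44 cases against 0.16 × 315 = 50 cases, while the users-only share goes down. In the equal-share rows the users-only comparison shows nothing, yet cases per patient are 0.90/0.70 = 1.29 times as frequent under the absolute reading, or 0.76/0.70 = 1.09 times under the relative one.

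**Size against sampling error (first row)**

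Users number 0.70 × 315 = 220.5 and 0.90 × 315 = 283.5. Ignoring clustering, the standard error is √(0.10 × 0.90/220.5 + 0.078 × 0.922/283.5) = 0.026. The shift of 2.2 points is thus about 0.9 standard errors.

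**The case against.** The strongest defence is that the users-only table answers a legitimate question. A method's risk category does not exist for someone using no method, Hypothesis 2 names no denominator, and the article calls the summary descriptive. It also uses the categories to choose interviewees and to build a joint display. Counting nonusers as not using Category 3 changes the question: with an identical share among users, the per-patient rate still goes from 7% to 9% simply because more people use a method. This stands, and it is why both tables are needed. It does not rescue the chi-square as the comparison for Hypothesis 2. That hypothesis is stated as a directional difference between arms, and even if a share among users was meant, randomization would not protect the comparison.

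The size is also modest and rests on assumed rates. A shift of about 0.9 standard errors is unlikely to give a false significant result by itself. If existing users do not change and use increases, the share among users can rise only when added users choose Category 3 more often than existing users do, which is a real increase in cases (last row of the table). Under these assumptions the distortion is dilution or a wrong sign against Hypothesis 2, not a spurious confirmation of it.

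A reader might infer more than the article supports:

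- That the share can move with nobody's choice changing. It cannot in these examples: under the absolute reading, 20% of patients move from no method to a method.
- That a single test over four categories is planned, which a shift between Categories 1 and 2 could make significant. The article speaks of tests in the plural and does not fix the contrast, and the analysis plan, not shown, may do so.
- That the sexual-activity subgroup also fails to test Hypothesis 2. It is listed as an analysis of nonuse and belongs to Hypothesis 1.
- That this subgroup is shown to be biased. It is defined by "those who report penile-vaginal sexual activity at 1 month and 3 months", reported after allocation by unblinded patients, so an effect of the tool on membership is possible, but nothing in the article shows one. Requiring activity at both times is only one reading, since the sentence also covers the 1-month model.

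**Conclusion.** The point holds for the US MEC comparison. The article states an analysis whose denominator is set by the primary outcome and which does not directly measure what Hypothesis 2 predicts. If Hypothesis 1 is true, the users-only share can fall with no change in Category 3 use per patient (10% to 7.8%, or to 9.2% under a relative effect), or fall while use per patient rises (20% to 17.8% against 14% to 16%). These figures depend on carrying baseline nonuse forward to 3 months in the control arm, on how the 20% is read, and on illustrative Category 3 rates. The mechanism needs only that the tool changes who uses a method.

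The at-risk subgroup is a lesser and less certain matter: its membership could be affected by the intervention, and no size can be given. The primary analysis is not touched by either point.

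**What to change.** - Make the Hypothesis 2 comparison Category 3 use, yes or no with nonuse counted as no, among all enrolled patients by arm. Use the clinic-clustered mixed model already specified for the primary outcome, with a two-sided test.
- Report Category 4 over the same denominator, descriptively if events are too sparse for the model.
- Keep the users-only table, labelled as descriptive and not a randomized comparison. Show the two side by side, because the per-patient measure also reflects the change in overall use.
- Label the at-risk subgroup exploratory, or add a version defined by sexual activity at baseline.

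The cost is wording in the protocol and analysis plan, plus one baseline survey item if sexual activity is not already asked. The Category 3 comparison needs no new data and no change in sample size. The downside of a baseline definition is that activity then may be a poor marker of risk at 3 months, for example in postpartum patients, who are explicitly eligible.

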### Randomization Process, Allocation Concealment, and Blinding

To avoid potential contamination across providers and patients, we will randomize by clinic site.

Clinics will be randomized in even-numbered blocks (2,4) to ensure balanced allocation of group conditions. The lead biostatistician (AS) will generate the allocation sequence and assign clinics to the intervention arm or control arm. Due to the cluster-randomized design, allocation concealment is impractical, and it will not be possible to blind patients or clinicians. The study team will remain blinded to the group assignment when evaluating outcomes.

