The exploratory outcomes are hypothesized mediators of the intervention effect on the primary and secondary outcomes. First, contraceptive decisional conflict will be assessed with the DCS, a 16-item validated scale with 4 subscales [29] (0=no conflict; 100=greatest conflict). We slightly modified the wording of DCS items, when appropriate, to reflect contraceptive decisions rather than generic health decisions. Second, we will assess patient-reported quality of interaction with their contraceptive provider via the IQFP [30]. The IQFP contains 11 items that are assigned a score of 1-5 (1=poor, 2=fair, 3=good, 4=very good, and 5=excellent) by the patient to assess their clinician’s shared decision-making and interpersonal skills (total scores ranged from 11 to 55). We will conduct a mediation analysis as described by Baron and Kenny [53] with two models: (1) a logistic regression of the mediator (ie, DCS or IQFS, dichotomized) as a function of the primary outcome (contraceptive nonuse at 3 months), with a covariate for intervention versus control group, and (2) a logistic regression of the primary outcome (contraceptive nonuse at 3 months), adjusting for both the mediator (ie, DCS or IQFPS, dichotomized) and intervention versus usual care group.

We will conduct descriptive analyses on other patient, clinician, and clinic-level exploratory measures and statistical comparison tests as appropriate (eg, chi-square, Fisher exact, and *t* tests).

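### The chi-square tests planned for the US MEC category outcome take no account of clinic randomisation, so their false-positive rate would be well above nominal (about 12–26% for a two-category test, on stated assumptions)

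*Protocol article*

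**What the plan says.** The unit of allocation is the clinic: "To avoid potential contamination across providers and patients, we will randomize by clinic site" (Randomization Process, Allocation Concealment, and Blinding). The sample size allows for this. It cites an earlier cluster trial that "found a clinic-level intracluster correlation (ICC) of 0.02", then adopts a larger value, "We conservatively estimate an ICC of 0.05", and concludes that "we will need to enroll 14 clinics (7 in each arm) and 45 participants in each clinic" (Power and Quantitative Sample Size).

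Under Quantitative Outcomes and Analysis, contraceptive nonuse is analysed with a mixed-effects logistic model that has random intercepts for clinic and for clinician within clinic. The same model is reused for nonuse at 1 month. The secondary outcome, US MEC Category 1 to 4 among patients reporting contraceptive use at 1 and 3 months, is summarised descriptively and then tested: "Chi-square tests will be calculated to compare frequencies between the intervention group and the usual care group". No random effect, design effect or cluster correction is attached to these tests.

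This outcome carries Hypothesis 2, that the tool will support careful discussion, "leading to more Category 3 use cases in the intervention arm than the control arm" (Quantitative Aims and Hypotheses).

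**The concern.** A standard chi-square test takes its variance from the number of patients. When whole clinics are assigned to an arm, differences between clinics in prescribing habits or case mix also contribute to the difference between arms. With only seven clinics per arm these do not average out. The test then uses a standard error that is too small and rejects a true null hypothesis too often.

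The article recognises this when sizing the trial and when modelling nonuse, but not for the outcome behind Hypothesis 2. An apparent shift in Category 3 use could reflect which clinics fell in which arm. Because Category 3 is also the focus of the interviews and the joint display, a false quantitative signal would carry over into the mixed methods interpretation.

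This is not a detail left to an unseen analysis plan: the article names a specific test, and that test does not fit the design.

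**Working it through.** **Inputs**
- Clinics: 14, 7 per arm, 45 participants each (Power and Quantitative Sample Size).
- ICC: 0.05 adopted; 0.02 from the earlier cluster trial; and "Prior studies have estimated ICCs generally <0.04 for patient-reported outcomes". None is given for US MEC category. I use 0.02–0.05, with 0.01 as a lower check.
- Users per clinic: the test is limited to users. Expected nonuse is 30% at baseline, and the target difference is 20%, read here as percentage points. Taking use between 70% and 90% gives 0.70 × 45 = 31.5 to 0.90 × 45 = 40.5 users per clinic (assumption).
- Level: none is stated. Two-sided 5% is assumed.

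**The plan's own figures.** 7 × 45 = 315 per arm. 315 × 1.15 = 362.25, rounded up to 363, which gives the stated 726. So 45 is the number per clinic after attrition. The sizing design effect is 1 + (45 − 1) × 0.05 = 3.2. Power and the 3-month rates are not stated. With 80% power and 50% versus 30% nonuse, 93 × 3.2 = 298 per arm, and 298/45 = 6.6, so 7 clinics. The stated clinic count is therefore consistent with a clustering allowance of this size.

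**Type I error of an unadjusted test.** With design effect DE = 1 + (m − 1) × ICC, where m is users per clinic:
- two categories (1 df): 2 × [1 − Φ(1.96/√DE)]
- four categories (3 df), same DE in every category: P(χ²₃ > 7.815/DE)

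Worked ends of the range:
- m = 31.5, ICC 0.02: DE = 1 + 30.5 × 0.02 = 1.61; 1.96/√1.61 = 1.54; error 12.2%.
- m = 40.5, ICC 0.05: DE = 1 + 39.5 × 0.05 = 2.975; 1.96/√2.975 = 1.14; error 25.6%.

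| Users per clinic | ICC | DE | 1 df | 3 df |
|---|---|---|---|---|
| 31.5 | 0.01 | 1.305 | 8.6% | 11.2% |
| 31.5 | 0.02 | 1.61 | 12.2% | 18.3% |
| 31.5 | 0.05 | 2.525 | 21.7% | 37.7% |
| 36 | 0.01 | 1.35 | 9.2% | 12.2% |
| 36 | 0.02 | 1.70 | 13.3% | 20.4% |
| 36 | 0.05 | 2.75 | 23.7% | 41.7% |
| 40.5 | 0.01 | 1.395 | 9.7% | 13.3% |
| 40.5 | 0.02 | 1.79 | 14.3% | 22.5% |
| 40.5 | 0.05 | 2.975 | 25.6% | 45.3% |

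The unadjusted standard error is too small by a factor of √1.61 = 1.27 to √2.975 = 1.72 over the 0.02–0.05 range.

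**Simulation check.** Seven against seven clinics with no true arm effect, beta-binomial outcomes and prevalences of 10%, 20% and 30%:
- 32 users per clinic: 11.8–12.3% (ICC 0.02) and 21.8–22.5% (ICC 0.05).
- 40 users per clinic: 14.0–14.4% and 25.4–25.6%.
- Essentially no clustering (32–40 users): 4.8–5.1%, so the inflation comes from the clustering.
- Four-category version (Dirichlet-multinomial): 18.3% (32 users, ICC 0.02) to 44.6% (40 users, ICC 0.05).

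**The case against.** The size of the error rests on borrowed inputs. The adopted ICC was chosen to size the trial on nonuse and is called conservative. US MEC category depends partly on each patient's own conditions and medications, so its ICC could be lower or higher. The article also says allocation will attend to the balance of obstetrics and gynecology clinics. That would remove some between-clinic variance from the arm comparison, and the formula ignores it. All of this stands. It makes the percentages conditional, but it does not make a patient-level test valid: even at ICC 0.01 the two-category error is about 9%.

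It is also fair that Aim 2 is largely descriptive and hypothesis-generating, and that the primary model already handles clustering. That limits the consequences. Even so, a test is named for an outcome with a stated between-arm hypothesis.

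Three stronger readings are tempting, and the document does not support them:
- A reader might put the two-category error at 27%, using the sizing design effect of 3.2. That needs all 45 patients per clinic, whereas this test is confined to users.
- A reader might infer that Hypothesis 2 goes untested because a four-category test can reject on Categories 1, 2 or 4. The text speaks of chi-square tests in the plural and does not fix one four-level test. A two-sided test of a directional hypothesis is not an error either.
- A reader might extend the charge to the exploratory comparisons. There the wording is "statistical comparison tests as appropriate (eg, chi-square, Fisher exact", an illustrative list that leaves room for a clustered method, so it is not evidence that patients will be treated as independent.

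**Conclusion.** The point holds. The chi-square tests named for the US MEC outcome do not fit a clinic-randomised design and are inconsistent with the article's own sizing and primary model. That they ignore clustering is read from their unqualified wording, next to a model where clustering is handled explicitly.

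For a two-category contrast the nominal 5% test would run at about 12–26%, and a four-category test at about 18–45%. These figures assume a two-sided 5% level, 70–90% users, and ICCs of 0.02–0.05 carried over from elsewhere. The four-category figure also assumes one design effect for all categories. They indicate how large the problem could be and are not known error rates. The test should be replaced before the secondary outcome is analysed; the design, the sample size and the primary conclusion do not depend on it.

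**What to change.** - **Hypothesis 2:** replace the chi-square test with a mixed-effects logistic model for Category 3 use (yes/no) among contraceptive users, with a clinic random intercept. Add the clinician intercept only if it can be estimated: 441 to 567 users (14 × 31.5 to 14 × 40.5) over 70 to 140 clinicians (14 × 5 to 14 × 10) is about 3 to 8 each.
- **Small number of clusters:** name a small-sample correction for 14 clusters, or use a cluster-level analysis on 14 − 2 = 12 df. A statistic that follows a t distribution with 12 df but is judged against 1.96 rejects about 7.4% of the time, so a random intercept alone may not restore 5%.
- **Four-level table:** if it is tested, use a cluster-adjusted chi-square of Rao-Scott type.
- **Category 4:** keep it descriptive if events are few.
- **Exploratory measures:** state that any inferential between-arm test will account for clinic clustering.

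The change is to wording in the analysis section, with no change to enrolment or data collection. The statistical cost is wider confidence intervals and lower power for the secondary outcome.
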